## Methods

### Participants

A total sample of 160 female participants will be recruited in Switzerland and Luxembourg. AN (restricting-type), BN (without history of AN) patients meeting DSM-5 (American Psychiatric Association, 2013) criteria will be divided into currently-ill (C) and recovered (R). Thus, C-AN (*n* = 30) and C-BN (*n* = 30) will be compared to R-AN (*n* = 20) and R-BN (*n* = 20) patients, as well as to two age-matched control (CT) groups: underweight (U-CT; *n* = 30) and normal-weight (N-CT; *n* = 30) without eating disorders. BN with previous history of AN or binge-eating/purging type of AN will be excluded to enable a better differentiation between these disorders. Participants will be asked to provide demographic information, height, weight, duration of illness, time in treatment, age at onset, duration of recovery where applicable, and self-reported salivary, metabolic, and/or otorhinolaryngologic disorders. Ethical permission was obtained from Swiss Ethics Committee and from the Ethics Review Panel of the University of Luxembourg. Participants will provide written informed consent.

### Inclusion and exclusion criteria

Principal inclusion and exclusion criteria are shown in Table 1.

**Table 1 T1:** Principal inclusion and exclusion criteria.

**INCLUSION CRITERIA**
**Normal and underweight control groups**
Female sex
Age from 18 to 35 years of age
Informed consent with understanding of the study and procedures
No eating disorder history
BMI < 18 (underweight subgroup) or 18.5 < BMI < 25 (normal-weight subgroup)
**Current anorexia and bulimia nervosa groups**
Diagnoses of AN (restricting-type without previous history of binge-eating/purging type) or BN (without history of AN)
If treatment has started, reduction of the initial eating disorder pathology measured by EDE-Q (Mond et al., 2004) <30%.
<50% of the target weight gain (AN) or <30% reduction of binge eating and compensatory episodes (BN)
**Recovered anorexia and bulimia nervosa groups**
Not meeting all criteria for an AN or BN at the time of discharge
BMI > 18 and a global EDE-Q-score <2.3 (Munsch, 2014)
**EXCLUSION CRITERIA**
Pregnancy or lactation
Psychotic and related disorders or depressive disorders*
Serious medical conditions having an effect on eating and mood
Lack of compliance with study procedure
Past bariatric surgery
Allergy for the foods offered
History of olfactory or gustatory pathology, and salivary, metabolic or otorhinolaryngologic disorders (e.g., ageusia, dysgeusia, anosmia, hyposmia, allergic rhinitis, chronic rhinosinusitis, and upper respiratory infection)

*Smoking (more than 5 cigarettes per week) and current intake of serotonin-specific reuptake inhibitors will not be initially considered an exclusion criterion, but will be recorded carefully. Phenylketonuric people will be appropriately warned as the high sweet samples content Aspartam, a source of Phenylalanin. *If they prevent a participation in the trial*.

### Ethical aspects and approval

The study was approved by the ethical committee of the leading center at the University of Fribourg (CER-VD, n° 2016-02150) as well as in the cantons of collaborating clinics in Switzerland and the Ethics Review Panel of the University of Luxembourg. Written informed consent in accordance with the Declaration of Helsinki will be obtained (Declaration of Helsinki). All procedures within this research project will be conducted in accordance with the guidelines for Good Clinical Practice by clinically trained investigators under the permanent supervision of the main applicants. All data will be coded without personal identifiers to ensure confidentiality. Participants may withdraw from the trial at any point without any penalty.

### Procedure: recruitment, sample characterization, and experimental session

The procedure is summarized in Figure 2. The participant recruitment process starts with a recruitment letter to inform female patients between 18 and 35 years of age, starting or finishing with treatment, about our study at the collaborating clinics or with advertising flyers in public places and at the University in the case of healthy control participants. If the patient agrees, and after obtaining informed consent and the authorization to release/exchange confidential information, they will be contacted by phone to set three appointments in weekly intervals. During the first week, a diagnostic interview will be carried out by telephone. Eligible participants will be required to fill out a set of online questionnaires (LimeSurvey; www.limesurvey.org), including the General Health Questionnaire, EDE-Q, short form of the Beck Depression Inventory-II (BDI-II), Food Cravings Questionnaire—Trait (FCQ-T-reduced) and Thought-Shape Fusion Questionnaire (TSF-Trait) (see Table 2) during the second week. Finally, the experimental session in the clinics or in the psychophysiological laboratory at the universities of Fribourg and Luxembourg are expected in the third week. In the case of healthy controls, the procedure will be the same except for the diagnostic interview.

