**Figure 2 F2:**
[figure not shown]
Flow graph of the procedure.

**Table 2 T2:** Summary of the measures, instruments and outcomes.

**Type**	**Measure/instrument**	**Measure description**	**Device/author**	**Outcome**	**Study**
Subjective	Diagnostic interview for psychiatric disorders (**Mini-DIPS**) and Structured Clinical Interview for DSM-IV (**SCID-I**)	Structured interviews to assess psychiatric disorders according DSM-IVTR and DSM-5	Wittchen et al., 1997; Schneider and Margraf, 2011	Diagnostic phase	Study 1 & 2
	Eating Disorder Examination Questionnaire (**EDE-Q**) (score)	36 items scored on a 7-point Likert-type scale reporting restraint, eating concerns, weight concerns and shape concerns, as well as frequencies of compensatory behaviors are also self-reported. Internal consistency >0.70; test-retest reliability >0.50	Mond et al., 2004	Diagnostic phase	Study 1 & 2
	Thought-Shape Fusion Body State Scale (**TSF-B state**)	5-item questionnaire assessing body-related cognitive distortions according to Radomsky et al., 2002. Each item rated on a 100-mm VAS scale (0–100). Cronbach's alpha = 0.86	Wyssen et al., 2016	Baseline	Study 1 & 2
	Beck Depression Inventory-II (**BDI-II**) (score)	21 items rated in a 3-point scale indicates depression raging from normal mood to severe depression. Internal consistency >0.90; test-retest reliability >0.90; convergent validity >0.71	Beck et al., 1996	Baseline	Study 1 & 2
	Food Cravings Questionnaire—Trait (**FCQ-T-reduced**) (score)	15 items scored on a 6-point scale related with eating pathology, body mass index, low dieting success and increases in state food craving during cognitive tasks involving appealing food stimuli. Internal consistency >0.70; validity demonstrated by positive correlations between scores on the FCQ-T-r, BMI and cue-elicited FC; convergent validity >0.50	Meule et al., 2011	Baseline	Study 1 & 2
	Thought-Shape Fusion Questionnaire (**TSF-Trait**) (score)	18 items which measures the susceptibility to body-related cognitive distortions	Coelho et al., 2013; Wyssen et al., in press	Baseline	Study 1 & 2
	The Brief Mood Scale (**BMS**)	8 bipolar items on a 100-mm VAS (0–100). Cronbach's alpha >0.88	Wilhelm and Schoebi, 2007	Baseline	Study 1 & 2

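### Controls skip the only structured diagnostic interview and have no EDE-Q limit, so an undetected restrictive case could enter the underweight control group

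*Protocol article*

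**What the plan says.** All places are in the protocol article.

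- **Procedure section.** Patients have a telephone diagnostic interview in week 1, online questionnaires including the EDE-Q in week 2, and the tasting session in week 3. For the questionnaires it says: "Eligible participants will be required to fill out a set of online questionnaires". For controls it says: "In the case of healthy controls, the procedure will be the same except for the diagnostic interview".
- **Table 2.** The interviews (Mini-DIPS and SCID-I) are described as "Structured interviews to assess psychiatric disorders according DSM-IVTR and DSM-5". The EDE-Q covers restraint and eating, weight and shape concerns, "as well as frequencies of compensatory behaviors are also self-reported". Both carry the label of the diagnostic phase.
- **Participants and Table 1, controls.** Both control groups are "without eating disorders" and must have "No eating disorder history". BMI must be below 18 for U-CT, and between 18.5 and 25 for the normal-weight controls (N-CT). No EDE-Q value is given.
- **Table 1, patients.** Recovered patients need a BMI above 18 and "a global EDE-Q-score <2.3". Current patients already in treatment must show less than a 30% reduction in initial EDE-Q pathology.
- **Abstract.** Both control groups are described as having no eating-disorder pathology of any kind.

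**The concern.** The interview is the only structured diagnostic tool in the study, and dropping it for controls is a stated choice. What remains is a criterion about history, with no described way of establishing it, and a questionnaire with no score at which a control is excluded. A control could therefore score above the level that disqualifies a recovered patient.

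The gap matters most in U-CT. H1 attributes perceptual disturbance to cognitions about weight gain and not to BMI, and the Procedure section relies on under- and normal-weight controls to separate low BMI from psychopathology. In U-CT low weight is the entry criterion, so it cannot raise suspicion of a restrictive disorder. If some of these women have an undetected restrictive disorder, the group no longer shows the effect of low BMI alone.

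**Working it through.** **1. EDE-Q rules by group (Table 1).**

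| Group | Structured interview | EDE-Q rule |
|---|---|---|
| Current AN, BN | yes | less than 30% reduction, if treated |
| Recovered AN, BN | yes | global score below 2.3 |
| U-CT, N-CT | no | none stated |

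**2. Is there another low-weight comparator without an eating disorder?** Recovered groups need BMI above 18 and N-CT above 18.5. Only U-CT lies below 18.

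**3. Effect on the C-AN versus U-CT contrast.** The plan gives no figure to reproduce. Inputs: 15 U-CT per study (Sample size calculation), k undetected cases among them, and r, the fraction of the C-AN response that each shows. The documents give neither k nor r, so both are assumptions. Let D be the true difference between C-AN and genuine U-CT.

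Observed U-CT mean = genuine U-CT mean + (k/15) × r × D

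Observed difference = D × (1 − r × k/15), so the shrinkage is r × k/15.

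| k | r = 0.5 | r = 1 |
|---|---|---|
| 1 | 0.5 × 1/15 = 3.3% | 1/15 = 6.7% |
| 2 | 0.5 × 2/15 = 6.7% | 2/15 = 13.3% |
| 3 | 0.5 × 3/15 = 10.0% | 3/15 = 20.0% |

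As an illustration of power, take 15 v 15, a two-sided 5% test and an assumed standardised difference of 1.0. Three fully AN-like cases cut the difference to 1.0 × (1 − 0.2) = 0.8, and power falls from 78% to 59%. Starting from 0.8, the difference becomes 0.64 and power falls from 59% to 42%.

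**4. Direction.**
- *Response bias and disgust (H1, H2):* a difference is predicted, so shrinkage works against the hypothesis.
- *d′ (H1):* similar performance is predicted. If C-AN had a real deficit, contamination would shrink it by the same factor, which favours the prediction.
- *U-CT versus N-CT:* the U-CT mean moves by r × k/15 of D towards C-AN. If low BMI has no effect, three fully AN-like cases would still separate U-CT from N-CT by 20% of D, which could be read as an effect of BMI.

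**5. Does the covariate repair this?** The Planned analysis adjusts for EDE-Q. That adjusts the outcome for the score but leaves a misclassified woman in the control group. The effect on the adjusted contrast cannot be computed from the documents.

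**The case against.** The strongest reply is that the control criteria already bind. Controls must have no eating disorder history, they complete the EDE-Q a week before tasting, Table 2 assigns that form to the diagnostic phase, and clinically trained investigators run the procedures under supervision. Table 1 lists only principal criteria, and the flow chart in Figure 2 is not shown and could contain a screening step. This stands in part. That the history is self-declared is an inference: the text describes no other source but does not rule one out. A reader might infer that controls are not screened at all, or that women with eating disorders are admitted knowingly. The documents support neither.

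A second reply is that a cut-off on another self-report form does little against concealment. It was also set for recovery, not for never-ill underweight women. It may remove women with high weight concern but no disorder, which would select lower-concern controls and reduce EDE-Q overlap with patients in the adjusted analysis. This also stands, and it is why the fix below offers a second route.

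A third reply is that contamination is conservative and therefore harmless. That holds for the predicted differences in response bias and disgust between C-AN and U-CT. It does not hold for similar d′ or for the U-CT versus N-CT comparison. H1 and H2 also use N-CT and the recovered groups, which limits the damage, but neither matches C-AN on low weight.

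**Conclusion.** The point holds as a gap in how control status is verified. Controls are exempt from the only structured interview, the EDE-Q has no limit for them although it has one for recovered patients, and the text describes no other check. An undetected restrictive case could therefore enter U-CT.

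The size is unknown. The range of 3.3% to 20% shrinkage rests on assuming one to three cases among 15, each responding half-way to fully like C-AN, and applies to the unadjusted contrast only. The documents do not show that any such case will be enrolled, and the power figures also assume an effect size. A reader might infer that the C-AN versus U-CT comparison is invalid or that false-positive differences in response bias or disgust would follow. The text supports neither, since contamination pulls those contrasts towards zero. Priority is minor to moderate: the main low-weight comparison is affected, but the likely loss is modest and the remedy is cheap.

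**What to change.** Add to Table 1 a global EDE-Q below 2.3 for both control groups, score the week-2 form before the week-3 session, and replace controls who fail. To avoid losing never-ill women with high weight concern, a score of 2.3 or more may instead trigger the eating-disorder section of the existing telephone interview, with exclusion only if a disorder is found.

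The first route needs no new questionnaire or visit and leaves the sample size at 80 per study. It costs some replacement controls; how many is unknown, because the documents give no failure rate and no recruitment rate for women with BMI below 18. The second route adds one short call for each control at or above the limit. Under both, the first screen is still self-report and uses a value chosen for recovery. The first may also leave controls with slightly lower weight concern.

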**Figure 2 F2:**
[figure not shown]
Flow graph of the procedure.

**Table 2 T2:** Summary of the measures, instruments and outcomes.

**Type**	**Measure/instrument**	**Measure description**	**Device/author**	**Outcome**	**Study**
Subjective	Diagnostic interview for psychiatric disorders (**Mini-DIPS**) and Structured Clinical Interview for DSM-IV (**SCID-I**)	Structured interviews to assess psychiatric disorders according DSM-IVTR and DSM-5	Wittchen et al., 1997; Schneider and Margraf, 2011	Diagnostic phase	Study 1 & 2
	Eating Disorder Examination Questionnaire (**EDE-Q**) (score)	36 items scored on a 7-point Likert-type scale reporting restraint, eating concerns, weight concerns and shape concerns, as well as frequencies of compensatory behaviors are also self-reported. Internal consistency >0.70; test-retest reliability >0.50	Mond et al., 2004	Diagnostic phase	Study 1 & 2
	Thought-Shape Fusion Body State Scale (**TSF-B state**)	5-item questionnaire assessing body-related cognitive distortions according to Radomsky et al., 2002. Each item rated on a 100-mm VAS scale (0–100). Cronbach's alpha = 0.86	Wyssen et al., 2016	Baseline	Study 1 & 2
	Beck Depression Inventory-II (**BDI-II**) (score)	21 items rated in a 3-point scale indicates depression raging from normal mood to severe depression. Internal consistency >0.90; test-retest reliability >0.90; convergent validity >0.71	Beck et al., 1996	Baseline	Study 1 & 2
	Food Cravings Questionnaire—Trait (**FCQ-T-reduced**) (score)	15 items scored on a 6-point scale related with eating pathology, body mass index, low dieting success and increases in state food craving during cognitive tasks involving appealing food stimuli. Internal consistency >0.70; validity demonstrated by positive correlations between scores on the FCQ-T-r, BMI and cue-elicited FC; convergent validity >0.50	Meule et al., 2011	Baseline	Study 1 & 2
	Thought-Shape Fusion Questionnaire (**TSF-Trait**) (score)	18 items which measures the susceptibility to body-related cognitive distortions	Coelho et al., 2013; Wyssen et al., in press	Baseline	Study 1 & 2
	The Brief Mood Scale (**BMS**)	8 bipolar items on a 100-mm VAS (0–100). Cronbach's alpha >0.88	Wilhelm and Schoebi, 2007	Baseline	Study 1 & 2
	**Ratings**: sweetness and fattiness identity and intensity (score) **SDT parameters**: d′ (sensory sensitiviy), C and ß (response bias based on cognitive strategy)	11-point anchored Likert-type scale (scores from 0 to 10) designed to measure taste perception	Sussex Ingestion Pattern Monitor (SIPM™ 2.0); Sussex University; UK	Primary	Study 1
	**Ratings**: pleasantness of the taste (score)/thirst and hunger level (score)/familiarity of food samples.	Time-intensity measures for pleasure; opportunity to scale the perceived liking dynamically over 60 sec. Labeled magnitude scale for thirst/hunger	SensoMaker™; UFLA, Brazil	Primary/secondary	Study 1 & 2
Behavioural	**Facial expressions**: general emotions, valence and actions units (intensity score)	Positive/negative valence as measure of overall affection; general emotions (joy, anger, surprise, fear, contempt, sadness, disgust); action units as the likelihood of specific facial muscle activations	FACET™ SDK; iMotions Inc., Cambridge Innovation Center, US	Primary	Study 1 & 2
Psycho-physiological	**Cardiovascular**: heart rate and heart rate variability	Cardiovascular Changes as index of cardiac sympathetic activation and autonomic arousal	Module—GSR & Heart Rate and ECG/EMG; Shimmer3 EMG/ECG, GSR Kit and EXG Devices; iMotions Inc., Cambridge Innovation Center, US	Primary	Study 2
	**Electrodermal activity**: skin conductance level (μmhos), skin conductance response rate (count/min)	Changes in the conductivity of skin as index of sympathetic activation		Primary	Study 2
	**Facial electromyography**: EMG powers (mV)	EMG activity of the levator labii (disgust), corrugator supercilia (general negative affect) and zygomatic major (pleasure) muscle regions		Primary	Study 2

The experimental session will be composed of assessments of thirst and hunger levels, the Thought-Shape Fusion Body State Scale (TSF-B state) and Brief Mood Scale (BMS) questionnaire, a training session to habituate to the testing environment and apparatus, and either the discrimination of two-alternative forced-choice (2AFC) test in study 1 or multiple-sip temporal-liking (MSTL) with taste reactivity (TR) task in study 2. Each experimental session will take around 1.5 h. Concerning the first study (Table 3), the 2AFC test with signal detection theory (SDT) analysis will be used as it provides a high level of power for small food differences and low levels of response bias (Hautus et al., 2009). On the one hand, the 2AFC test is a psychophysical method in which participants are required to select the one of two food samples, which represents the specified attribute best (e.g., the sweeter one). On the other hand, SDT is a sophisticated tool that permits to understand the information processing that takes place in the brain during sensory discrimination testing, providing an accurate index of perceived sensory differences and efficient characterization of cognitive strategy. Therefore, SDT is critical for investigating maladaptive cognitions involved in the processing of received taste information, which affects sensory testing (Smeets et al., 2008). Furthermore, whether and how much gustatory performance depends on low BMI or psychopathology will be examined including under- and normal-weight controls and patients at different stages of the disorder (currently-ill vs. recovered). Finally, in addition to the sip-and-spit condition, a swallow test condition will be included (Eiber et al., 2002) to enhance cognitive bias toward weigh gain underlying the fear of swallowing and quantify the impact of these biased cognitions on gustatory performance. The 2AFC task will be conducted using the SIPM™ software (Sussex Ingestion Pattern Monitoring, version 2.0.11), in which pairs of two samples (with varying levels of sweetness and fatness), presented simultaneously at each trial, are judged in terms of taste identity and intensity (see Table 2).

**Table 3 T3:** Experimental design of the study 1.

**Group**	**Pre-test**	**Test: two-alternative forced-choice task**	
		**Spit condition**	**Swallowed condition**
R-AN	Training session to habituate to the testing environment	A vs. B, A vs. C, A vs. D, B vs. C, B vs. D, C vs. D	A vs. B, A vs. C, A vs. D, B vs. C, B vs. D, C vs. D
C-AN			
U-CT			
N-CT			
R-BN			
C-BN			

*A, B, C, D, samples of ice cream with a high-/low-sweet and high-/low-fat taste. The order of the paired samples and conditions (swallow and spit) will be randomized. R-AN, recovered anorectic; C-AN, currently ill anorectic; U-CT, underweight control; N-CT, normal weight control; R-BN, recovered bulimic; C-BN, currently ill bulimic. R-AN and R-BN will be assessed at discharge*.

Concerning the second study (Table 4), a full-scale hedonic taste methodology using MSTL with TR will be applied to provide self-report, facial expression, facial electromyographic and autonomic measures to investigate (1) whether restrictive-type AN individuals respond with taste aversion for high-calorie foods and (2) if individuals with BN respond with excessive pleasure to sweet tastes. The MSTL and TR methodologies have been successfully employed previously with healthy populations (Rocha-Parra et al., 2016), showing both to be highly sensitive to detect small emotional variations when hedonic reactions are monitored dynamically via cumulative measurements, multiples sips and measurements at different durations. Consequently, this approach will allow for addressing two important unresolved issues: the temporal aspects of the hedonic response while eating (Delarue and Blumenthal, 2015), which have received no attention in EDs despite clinically observable aberrant emotional processing, and the scarce data on taste reactivity in EDs, which is considered the gold standard measure of hedonic aspect of human gustation without being limited by cognitive appraisal confounders of self-reports. MSTL, in which participants report subjective hedonic evaluations with SensoMaker™ software (version 1.8; Pinheiro et al., 2013) during 60 s while drinking three sips of each sample, taking one sip every 20 s, and TR measures (facial expression, facial electromyographic, electrodermal and heart rate reactivity) (Table 2) will be recorded while tasting food samples. The video files will be run through the FACET™ SDK (iMotions Inc., Cambridge Innovation Center, US), which is an automatic facial expression recognition software that tracks and analyzes frame-by-frame (1/25 s) valence, action units and emotions. Finally, the motivational component (i.e., desire to eat) of hedonic reward of each food sample will be also assessed at the end of the 60-s period, asking “How much do you want to eat this food?” Participants' responses will be monitored using a 20 cm unstructured line scale anchored at both extremes 0–100 on the monitor (0 = “not at all”; 100 = “extremely”). Finally, in order to even increase patients' safety and well-being the standardized procedure in clinics will be enlarged by a short muscle relaxation training session of 15 min offered to patients at the end of the experimental session for study 1/study 2 to reduce any anxiety raised by tasting chocolate ice cream samples.

**Table 4 T4:** Experimental design of the study 2.

**Group**	**Pre-test**	**Test: multiple-sip temporal-liking and taste reactivity**	
		**Spit condition**	**Swallowed condition**
R-AN	Training session to habituate to the testing environment	3 sips × water, 3 sips × A, 3 sips × B, 3 sips × C, 3 sips × D, 3 sips × E, 3 sips × F	3 sips × water, 3 sips × A, 3 sips × B, 3 sips × C, 3 sips × D, 3 sips × E, 3 sips × F
C-AN			
U-CT			
N-CT			
R-BN			
C-BN			
			

*A, B, C, D, samples of ice cream with a high-/low-sweet and high-/low-fat taste. E, F, samples of savory high-fat and low-fat sauces, respectively; R-AN, recovered anorectic; C-AN, currently ill anorectic; U-CT, underweight control; N-CT, normal weight control; R-BN, recovered bulimic; C-BN, currently ill bulimic. R-AN and R-BN will be assessed at discharge*.

